#### Intervention phase

The 12-week intervention consisting three components: a) three monthly group education sessions (10 participants in each group), b) three monthly center-based supervised group exercises (10 participants in each group), and c) individualized telephone follow-up will be conducted 1 week after the preparatory phase to transform the intention into action and to maintain the behavioral change. The intervention will be delivered as follows.

*Weeks 1–4*. ***Week one (day one)***: To facilitate an individual’s behavioral change, a 40-min face-to-face group education on nature, risk factors, signs and symptoms, and management of CHD and medication adherence will be delivered by the researcher at the hospital’s cardiology clinic. The educational booklet consisting the following topics: nature of CHD, risk factors, signs and symptoms of CHD, heart-healthy diet, physical activity, quitting smoking, stress management, and medication management and adherence. This booklet was developed based on the updated international guideline and culturally appropriate national recommendation for CHD [29–36] and validated by an expert panel consisting of registered physiotherapists, registered nutritionists, cardiologists, and the cardiac nurse for their safety and appropriateness for patients with CHD in Sri Lanka. This booklet will be given to the participants on day one to provide culturally relevant written resources to encourage the patients to follow the health advice at home. The knowledge gained in the education will help the participants form the intention by increasing risk perception, positive outcome expectancies, and self-efficacy in the motivational phase of HAPA. In addition, the education will support the participants in planning the action of intended behavior and help in maintaining self-efficacy throughout the volitional phase of HAPA.

Apart from the group education, a hospital plus home-based heart-healthy exercise will be implemented by the researcher with the support of a physiotherapist, registered nurse, and medical officer at the study hospital’s cardiology clinic. On day one in the first week of the intervention, participants will be guided to perform the exercise (warm-up exercise, brisk walking, and cool-down exercise) with cultural background music (Raravenu Gopabala Instrumental flute version) to perform the exercise at the prescribed intensity and duration and reduce the rating of perceived exertion during exercise [37, 38] under the supervision of a physiotherapist. As suggested by the cardiologist, the exercise will start at low intensity with cultural background music with a slow tempo (40–60 beats per minute). The participants will be guided to perform the warm-up exercise for 5 min before walking. Then participants will be asked to walk for 20 min with the speed paced by the music tempo of Raravenu Gopabala Instrumental flute version. After completing the walking exercise, the participants will perform the cool-down exercise for 5 min.

The participants will be asked to continue the exercise at home with the same duration and intensity performed on day one in the first week of the intervention at the hospital with culturally background music at least three times per week. On day one, an exercise logbook will be distributed to the participants, and the researcher will teach them how to fill the logbook and how to follow the exercise plan for home-based practice. This exercise log record will allow the participants to self-monitor and track their exercise practice at home to maintain the action and coping plan of the HAPA.

***Week three (days 15–22)***: The researcher or trained research assistant will provide a 20-min telephone follow-up at week three to strengthen the volition of the participant in performing the exercise, following the healthy diet at home, enhancing problem-solving skills in overcoming perceived barriers and providing reinforcement for any resulting positive changes. In each telephone follow-up, the goal and action plan will be reviewed and mutually adjusted as necessary for the next follow-up review.

*Weeks 5*–*8*. ***Week five (day one)***: Forty-minute face-to-face group education on physical activity and a heart-healthy diet will be delivered by the researcher at the hospital’s cardiology clinic on day one of the fifth week of the intervention. Apart from group education, participants will be guided to perform the exercise with the same duration and intensity performed in the first session on day one in the first week of the intervention (warm-up exercise: -5 min, brisk walking: -20 min, and cool-down exercise: -5 min) with cultural background music with a slow tempo under the supervision of a physiotherapist. In addition, participants will be advised to continue the exercise at home with the same duration and intensity performed on day one in the fifth week of the intervention at the hospital with cultural background music at least three times per week. Participants will be asked to complete the exercise logbook to determine the progress of the exercise.

***Week seven (days 43***–***50)***: A 20-min telephone follow-up at week seven will be provided by the researcher or trained research assistant with the same objectives as the telephone follow-up at week three.

*Weeks 9*–*12*. ***Week nine (day one)***: Forty-minute face-to-face group education on how to quit smoking and stress management will be delivered by the researcher at the hospital’s cardiology clinic on day one of the ninth week of the intervention. Apart from the group education, participants will be guided to perform the exercise with moderate intensity (warm-up exercise: -5 min, brisk walking: -30 min, and cool-down exercise: -5 min) with cultural background music under the supervision of a physiotherapist. In addition, participants will be advised to continue the exercise at home with the same duration and intensity performed on day one in the ninth week of the intervention at the hospital with cultural background music at least three times per week until the end of the 12-week intervention. Participants will be asked to complete the exercise logbook to determine the progress of the exercise.

***Week 11 (days 61***–***67)***: A 20-min telephone follow-up at week 11 will be provided by the researcher or trained research assistant with the same objectives as the telephone follow-up at week three.

### Usual care

Participants in both groups will receive the usual care services for patients with CHD provided in the study hospital. For example, an unstructured health education conducted by a nurse on a healthy lifestyle (exercise, heart-healthy diet, stress management, and smoking cessation) will be given once a month for 1 year after discharge through face-to-face sessions. During the first visit of the patient with CHD to the cardiology clinic 2 weeks after discharge, the cardiologist will assess the patient’s condition and provide brief unstructured health education on their conditions, focusing on risk factor management and stress management for 10–15 min. The patients will also be instructed to visit the cardiology clinic every month for medical follow-up.

### Data collection

The primary outcome of this study is the physical activity of the participants, whereas the secondary outcomes are cardiac exercise self-efficacy and cardiovascular risk factors, namely, body weight, BMI, waist-hip ratio (WHR), blood pressure, serum lipid levels, and fasting plasma glucose level. Physical activity, cardiac exercise self-efficacy, body weight, BMI, WHR, blood pressure, and fasting plasma glucose will be measured at baseline, immediate post-intervention, and one-month post-intervention, whereas the lipid profile will be measured at baseline and immediately after the intervention.

#### Socio-demographic and clinical data

Socio-demographic and clinical data will be collected at baseline to identify the factors that may influence the outcomes of this study. The socio-demographic characteristics, including gender, age, marital status, ethnicity, education level, employment status, and monthly family income, will be collected from the participants. Clinical characteristics, including duration of illness, medication history, and other comorbidities, will be collected from their medical records.

#### Primary outcomes

*Physical activity*. The primary outcome of the study is a behavioral change, which is physical activity. Physical activity refers to body movements that result in energy expenditure [39]. The International Physical Activity Questionnaire Short Form (IPAQ-SF) will be used in collecting the self-reported time spent in walking, moderate, and vigorous activities lasting at least 10 min, and time spent in sitting using the seven items [40]. The original English version of IPAQ-SF demonstrated high reliability with test-retest reliability ranging from 0.32 to 0.88 with more than three-quarters of studies showing a value greater than 0.65 [40]. The validated Tamil version of IPAQ-SF will be used in assessing the self-reported time spent in walking, moderate and vigorous-intensity activities, and sitting in this study.

#### Secondary outcomes

*Exercise self-efficacy*. Self-efficacy refers to an individual’s confidence to perform the given task and is a key indicator of behavioral change [41]. Self-efficacy is an important determinant of physical activity, and individuals with higher self-efficacy are likely to engage more in physical activities [42]. Cardiac Exercise Self-Efficacy Instrument (CESEI) will be used to assess the exercise self-efficacy of participants in this study. The original English version of CESEI is a 16-item unidimensional instrument that was developed by Hickey et al., in 1992 to assess an individual’s confidence to perform the exercise in different circumstances in cardiac patients [43]. Each item is rated on a five-point Likert scale from 1 (very little confidence) to 5 (quite a lot of confidence). Participants will be asked to rate their confidence level in performing exercises in various situations such as “fitting exercise into a busy day,” “exercising without getting chest pain,” “taking own heart rate before and after the exercise,” and “enduring light exercise.” The CESEI score ranges from 16 to 80, and a high score indicates a high level of self-efficacy in performing the exercises. The original English version of CESEI demonstrated good internal consistency with Cronbach’s alpha 0.97 and test-retest reliability with an intraclass correlation coefficient of 0.87 in a sample of CR patients [43]. Furthermore, significant known-group validity is found in exercise self-efficacy between marathon runners and CR patients (p = 0.04) [43]. The exercise self-efficacy level of participants will be measured using a validated Tamil version of CESEI.

*Cardiovascular risk factors*. ***Anthropometry***: All anthropometric measurements will be performed by a trained research assistant who will be blinded to the group allocation of participants. The weight will be measured with a calibrated mechanical personal scale (model-CAMRY, model number-BS 20140). Participants will be weighed wearing light clothes, without shoes, and an empty bladder. The height will be measured in a standing position by using a flexible plastic tape (without shoes), and the BMI will be calculated as weight in kilograms divided by height squared in meters (kg/m^2^). Waist circumference will be measured using non-stretchable measuring tape at the approximate midpoint between the lower margin of the last palpable rib and the top of the iliac crest to the nearest 1 cm at the end of normal expiration. Hip circumference will be measured at the widest level over the greater trochanters using a flexible plastic tape to the nearest 0.1 cm. WHR will be estimated as waist measurement (cm) divided by hip measurement (cm).

***Blood pressure***: Blood pressure in a sitting position will be measured using a mercury sphygmomanometer (Dekamet model Code: 0125). Participants will be asked to rest for 15 min and no caffeinated food should be consumed or drink for 30 min before measuring the blood pressure.

***Serum lipid levels***: The participants’ total cholesterol, high-density lipoprotein, low-density lipoprotein, and triglyceride levels will be obtained from their medical records.

***Fasting plasma glucose***: The participants’ fasting plasma glucose levels will be obtained from their medical records.

#### Data analysis

Data will be analyzed using SPSS version 22.0 statistical software with a 5% significance level (two-sided; SPSSINC., CHICAGO, IL, USA). Data will be analyzed using descriptive and inferential statistics. Descriptive statistics with mean, standard deviation, range, frequency, and percentage will be used to describe the participants’ socio-demographic characteristics and clinical data. The normality of the data will be tested using the skewness and kurtosis statistics and graphically analyzed by normal Q-Q plots. An independent t-test will be used to compare the baseline characteristics of the intervention and control group for continuous variables while the Chi-square test will be used for categorical variables. The generalized estimating equation model will be used to test the hypotheses, and determine the significant differences across different time points (effect of time, group, and time x group interaction) with adjustment for potential confounding variables to obtain a more precise estimation of the intervention effect. By clinical judgment and statistical incomparability at baseline, the potential confounders will be selected in this study. Intention-to-treat analysis will be used as an approach in analyzing all participants in the final analysis according to the original assigned group, irrespective of the treatment received. If these assumptions are not met, the equivalent non-parametric statistics will be used to analyze the data.

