### Sample size estimation

The sample size estimation is based on the primary outcomes of the study, namely, the physical activity level. Referring to the findings of the literature review, the effect size on improving physical activity is from 0.5 [25] to 0.8 [26]. Therefore, the smallest effect size of 0.5 [25] will be considered in calculating the sample size for this study. To achieve a power of 1-β = 0.8 with a significance level of 0.05 (two sides) and account for 14% of the attrition rate [27] of the previous study, a total of 150 participants will be recruited in this study.

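### The time x group test estimates a difference in changes and leaves unused the precision available from baseline physical activity; the stated covariate adjustment does not recover it

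*Protocol article*

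**What the plan says.** Under Data analysis, hypothesis testing rests on a GEE model, which is meant to "determine the significant differences across different time points (effect of time, group, and time x group interaction) with adjustment for potential confounding variables". The stated reason for the adjustment is "to obtain a more precise estimation of the intervention effect". Confounders are to be chosen by clinical judgment and by baseline differences between the arms. Baseline physical activity is not named as a covariate.

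Under Data collection, physical activity is measured at T0, T1 (after the 12-week intervention) and T2 (one month later). Lipids are measured at T0 and T1 only.

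Under Sample size estimation, "The sample size estimation is based on the primary outcomes of the study, namely, the physical activity level", and "the smallest effect size of 0.5 [25] will be considered in calculating the sample size for this study". With 80% power, a two-sided 5% level and 14% attrition, the total is 150. No test, visit, SD basis or correlation is given.

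Under Primary outcomes, the questionnaire is credited with "test-retest reliability ranging from 0.32 to 0.88". The same sentence adds that more than three-quarters of the studies found a value above 0.65.

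**The concern.** The article does not say outright that T0 belongs to the outcome vector, but the text points that way. One GEE sentence covers all outcomes, and lipids have only T0 and T1, so a time x group term for lipids cannot exist unless T0 is an outcome. Of the three listed effects, only time x group isolates treatment. The group term is either the T0 difference, which is zero in expectation after randomisation, or an average over visits diluted by T0.

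On that reading the treatment effect subtracts each patient's full baseline value, however weakly baseline predicts follow-up. Two things are at stake. First, precision is lost although the baseline value is already collected. Second, the adjustment that the article offers as its route to precision does not act on the term that carries the treatment effect. The power statement is also not tied to this contrast.

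**Working it through.** **Inputs.** From the article: d = 0.5, power 0.80, two-sided alpha 0.05, attrition 14%, N = 150, allocation 1:1, visits T0, T1 and T2. Assumptions: equal SD at all visits (set to 1); a baseline-to-follow-up correlation rho, which the article does not give and which is therefore shown over a range.

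**1. The plan's own figure.** For a plain two-sample comparison, the normal formula gives n = 2(1.960 + 0.842)²/0.5² = 62.8, so 63 per arm. The t-test needs 64 per arm. Inflating for attrition, 126/0.86 gives 147 and 128/0.86 gives 149, or 75 per arm = 150. The figure reproduces. Expected completers are 150 x 0.86/2 = 64.5 per arm, and power for a plain follow-up comparison is then 80.5% (t-test).

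**2. Variance of the two contrasts, per patient.**
- Difference in changes, T1 minus T0: 1 + 1 - 2rho = 2(1-rho).
- T1 adjusted for T0 as a covariate: 1 - rho².
- Ratio: 2(1-rho)/[(1-rho)(1+rho)] = 2/(1+rho), which exceeds 1 for every rho below 1.

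**3. Power with d = 0.5 in SDs of the follow-up value (assumption).** The effective standardised difference is 0.5 divided by the square root of the factor in step 2, with 64.5 per arm and a two-sided t-test.

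| rho | 2(1-rho) | 1-rho² | ratio | power, T1-T0 change | power, baseline-adjusted |
|---|---|---|---|---|---|
| 0.20 | 1.60 | 0.960 | 1.67 | 60.6% | 82.0% |
| 0.32 | 1.36 | 0.898 | 1.52 | 67.6% | 84.5% |
| 0.50 | 1.00 | 0.750 | 1.33 | 80.5% | 90.2% |
| 0.65 | 0.70 | 0.578 | 1.21 | 92.0% | 96.0% |

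The normal approximation gives the same figures to within about 0.7 percentage points.

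**4. Power with d = 0.5 in SDs of change.** The SD of change is then the unit of the effect, rho drops out, and power of the T1-T0 contrast is 80.5% at any rho. The variance ratio in step 2 is unaffected.

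**5. Effect of covariate adjustment on time x group.** With complete data, an identity link and time-constant covariates entered as main effects, a covariate shifts an arm's fitted mean by the same amount at every visit. The shift cancels in the change from T0, so the interaction estimate and its robust SE stay the same. Numerical checks agree:
- One three-wave data set with 130 patients and a strongly prognostic sex effect: interaction 0.0961 (SE 0.2520), both with and without sex in the model.
- Simulation with 64 per arm, complete data, an exchangeable GEE and 300 runs per rho: adding a time-constant covariate, or T0 physical activity itself, as a main effect changed the interaction by less than 1e-15.

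| rho | mean SE, time x group at T1 | mean SE, T1/T2 as outcomes with T0 as covariate | squared ratio |
|---|---|---|---|
| 0.32 | 0.204 | 0.165 | 1.53 |
| 0.50 | 0.174 | 0.151 | 1.33 |
| 0.65 | 0.146 | 0.133 | 1.21 |

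The squared ratios match 2/(1+rho).

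**The case against.** A reader might infer that the stated 80% power holds only if rho is at least 0.5, and that the trial is therefore probably underpowered. The documents do not support this, for three reasons.

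- **SD basis.** The threshold needs d = 0.5 to be in SDs of the follow-up value. The article says that "the effect size on improving physical activity is from 0.5 [25] to 0.8 [26", which could equally mean SDs of change, and then rho does not matter.
- **Choice of contrast.** A threshold near 0.5 belongs to the single T1-T0 contrast. On the same follow-up-SD basis, with equal variances and the same correlation between all visits, 80% power is reached at rho of about 0.32 for the mean of T1 and T2 minus T0. It is about 0.44 for a two-degree-of-freedom interaction test with equal effects at both visits, and about 0.58 if the effect halves by T2.
- **Likely correlation.** The lower end of the reliability range, 0.32, cannot be taken alone, because most of the studies exceed 0.65, where power is about 92%. Nor is test-retest reliability the correlation over a 12-week intervention, which may be lower. A shortfall is possible but not shown.

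It can also be said that T0 as an outcome is inferred, that the clause on precision is literally wrong only under the conditions in step 5 (14% attrition would allow small changes), that the time x group estimate is valid with no inflation of type I error, and that a condensed article may leave the primary contrast and covariate list to an analysis plan. All of this stands. It removes any claim of error in the sample size, and missing detail is not the point here. What remains is that the method as described is less precise than one using the same data, and that the reason given for adjusting does not apply to the treatment term.

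**Conclusion.** The point holds as an improvement to the stated method, not as an error in the sample size. On the natural reading, the treatment effect is an unbiased difference in changes whose variance is 2/(1+rho) times that of a baseline-adjusted analysis: 52% larger at rho 0.32, 33% at 0.5 and 21% at 0.65, assuming equal variances. This ratio does not depend on the SD basis of the effect size. The precision expected from covariate adjustment does not reach the time x group term when time-constant covariates enter as main effects; this is exact with complete data and an identity link.

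The consequence for power depends on what the documents leave open. With d in follow-up SDs, the T1-T0 contrast has between about 61% (rho 0.2) and 92% (rho 0.65), while baseline adjustment does not fall below the roughly 80% of a plain follow-up comparison at any correlation. With d in SDs of change, the T1-T0 contrast has about 80% throughout.

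**What to change.** Reword the analysis paragraph for physical activity. Take T1 and T2 as the outcomes, with visit, group, group x visit, baseline physical activity (x visit) and sex in the model; sex is already used to classify participants before randomisation. A longitudinal model with T0, T1 and T2 that constrains the T0 means to be equal across arms does the same job; use an unstructured covariance so that the weight given to baseline is estimated from the data.

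Name the adjusted group difference at T1 as the primary effect, state whether 0.5 is in SDs of the follow-up value or of change, and tie the 80% power statement to that contrast. For lipids, which have no T2 value, compare T1 between arms adjusted for T0. Replace the sentence on precision so that it refers to baseline adjustment of the follow-up values.

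The cost is rewording only: no new data, visits or patients. The change should be fixed before anyone sees outcome data by arm, because it determines the primary estimate.

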### Randomization, blinding, and data collection procedure

All eligible participants will be invited to participate in this study, and a thorough explanation of the study by using the information sheet will be provided by the researcher (Fig 1). Informed consent will be obtained from the participants by the researcher before the study begins. All eligible participants will be classified as either male or female because gender influences the level of physical activities among patients with CHD [28]. The participants will be randomized either to an intervention or control group with a ratio of 1:1 using block randomization with a block size of eight. Random sequencing for group allocation will be generated by an online application (http://www.randmization.com). The group allocation will be placed into an opaque sealed envelope and will be given to the participants after baseline data collection (T_0_) by the research assistant who is independent of the study. The participants will not be blinded to their group allocation because of the nature of the study. The outcomes will be evaluated after completiing the 12-week intervention (T_1_) and one-month post-intervention (T_2_) by a trained research assistant blinded to the participants’ allocation (Fig 2). The outcomes that will be evaluated are the physical activity level, exercise self-efficacy, and cardiovascular risk factors. Every participant will receive 230 Sri Lankan rupees (1 United States Dollar) after completing the data collection to compensate for their time spent on data collection.

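### Covariates for the primary GEE are selected partly by baseline significance tests, so the adjusted model follows chance imbalance instead of a fixed prognostic list

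*Protocol article*

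**What the plan says.** The Data analysis section first orders between-arm tests at baseline: "An independent t-test will be used to compare the baseline characteristics of the intervention and control group for continuous variables". Categorical characteristics, sex among them, get a chi-square test. It then specifies a generalised estimating equation with time, group and time x group effects as the hypothesis test, "with adjustment for potential confounding variables to obtain a more precise estimation of the intervention effect". The covariates for that model come from one sentence: "By clinical judgment and statistical incomparability at baseline, the potential confounders will be selected in this study". No covariate is named. The section does not say whether both criteria must be met or either is enough, or when the clinical judgment is made.

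The randomisation section gives sex a special role: "All eligible participants will be classified as either male or female because gender influences the level of physical activities among patients with CHD". Allocation then follows in a "ratio of 1:1 using block randomization with a block size of eight". Stratification by sex is the natural reading, although the text never uses that word.

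**The concern.** Under randomisation, a baseline difference between arms is a chance event. A t-test or chi-square test of that difference says nothing about whether the variable predicts physical activity, and prediction is what makes adjustment worthwhile. The rule therefore works against the stated aim of better precision: a strong predictor that happens to be balanced is passed over, and a weak one that happens to be imbalanced is taken in.

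The rule also sits badly with the design. If allocation is blocked within sex, the design itself prevents sex from becoming imbalanced. The testing criterion then cannot pick up the one variable that the protocol says influences the primary outcome.

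Finally, the covariate set of the primary model becomes known only after baseline data have been compared by arm. Unspecified clinical judgment alongside the tests does not close that gap, because no list binds it.

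**Working it through.** **Inputs from the protocol.** Total 150, standardised effect 0.5, power 0.80, two-sided alpha 0.05 and attrition 14% (Sample size estimation); 1:1 allocation in blocks of eight (randomisation section); seven socio-demographic and three clinical variables (Socio-demographic and clinical data). The male share, the correlations and independence between variables are assumptions.

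**Reproducing the sample size.** The t-test calculation gives 64 per arm; 64/(1 − 0.14) = 74.4, so 75 per arm and 150 in total. The stated figure is reproduced. About 150 × 0.86 = 129 completers are expected.

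**1. How often testing selects something.** With K independent tests at 5%, P(at least one) = 1 − 0.95^K.
- K = 10: 1 − 0.95^10 = 0.40.
- K = 22, if the 12 baseline outcome measures are also tested: 1 − 0.95^22 = 0.68.

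Any single variable is selected about 5% of the time, whatever its link to the outcome.

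**2. Whether testing can select sex.** With blocks of eight within sex, the arms differ by at most 4 in each stratum. For 90 men and 60 women, the worst case is men 44 v 46 and women 32 v 28:

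chi-square = 150 × (44 × 28 − 46 × 32)² / (90 × 60 × 76 × 74) = 0.28, against a critical value of 3.84.

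In 10,000 simulated allocations at each male share from 50% to 90%, the test was never significant; the largest chi-square was 1.78. If allocation were not stratified, sex would be selected about 5% of the time.

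**3. Cost for a post-baseline group comparison.** 8,000 simulated trials per setting, 129 completers, one covariate, linear model at a single time point:

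| Assumed correlation | Power, no adjustment | Power, adjust only if baseline p < 0.05 | Power, fixed adjustment | Type I error, test-based rule |
|---|---|---|---|---|
| 0.3 | 79% | 79% | 83% | 4.9% |
| 0.5 | 80% | 81% | 90% | 4.0% |
| 0.7 | 81% | 83% | 98% | 3.7% |

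The test-based rule recovers almost none of the available gain, and it is conservative where the covariate is strong. These figures apply only to this contrast.

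**4. The same question for the time x group contrast.** If baseline (T0) is one of the responses, the contrast is a difference in within-person change. A covariate that is constant over time and entered as a main effect cancels out of it when data are complete (linear model, exchangeable working correlation). In simulated fits the SE of time x group was 0.173 with sex and 0.173 without, while the SE of the group term fell from 0.182 to 0.172 when sex was added.

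**5. What the handling of baseline does.** With n per arm, unit variance and baseline-to-follow-up correlation r:
- T0 as a response (difference in change): SE = √(4(1 − r)/n).
- T0 as a covariate, T1 and T2 as responses: SE at T1 = √(2(1 − r²)/n).

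At an assumed r = 0.5 and n = 64 these are √(2/64) = 0.177 and √(1.5/64) = 0.153. Simulated fits gave about 0.173 and 0.151. The ratio is √((1 + r)/2), which is below 1 for any r below 1.

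**The case against.** The strongest reply has four parts.

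- **Clinical judgment is the first criterion named.** The protocol itself calls gender an influence on physical activity, so judgment is an obvious route for sex to enter. This stands. A reader might infer that sex will be left out of the model, but the text does not support that. It shows only that the test will not select sex and that nothing else guarantees it. Nor does the text say that judgment is applied after the imbalance is seen.
- **The power loss may not apply.** On the natural reading, the tested effect is time x group with T0 among the responses. Step 4 shows that a main-effect covariate then changes nothing with complete data. With 14% dropout and a covariate correlated 0.5 with the outcome, the mean SE moved only from 0.1715 to 0.1704. This also stands. A reader might infer that the trial falls from 90% to 81% power, or that omitting sex overstates the SE by about 5%. Both figures belong to a post-baseline group comparison under assumed correlations or variance shares, and the protocol does not say that this is the primary contrast.
- **No validity failure is shown.** This is correct. A reader might infer inflated type I error from data-driven selection, but the test-based rule gave 3.7% to 4.9%.
- **A covariate list often sits in a separate SAP.** The missing list is therefore not the point. The point is a rule that the protocol does state; a SAP that followed it would still select on imbalance.

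**Conclusion.** The concern holds in a limited form. Baseline significance testing is a stated selection criterion for the hypothesis-testing model. It picks variables by chance, at about 5% each and with a 40% chance of at least one among 10 independent variables. It almost never picks sex if allocation is blocked within sex, which the protocol implies but does not state. The adjusted model is therefore not fixed before the data are seen, whichever contrast is primary.

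The loss of precision is conditional. For a post-baseline group comparison, the rule forgoes most of the gain from a prognostic covariate (step 3). For time x group with T0 as a response and complete data, main-effect covariates give no gain to lose. There the precision available comes from how baseline physical activity is handled: an SE of about 0.15 instead of 0.17 to 0.18 at an assumed correlation of 0.5. All of these figures come from linear models with assumed correlations. The protocol does not say which GEE effect is primary, so no single figure for the loss can be given.

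**What to change.** Replace the covariate-selection sentence in Data analysis with wording that does the following:

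1. Keeps the baseline table descriptive and drops baseline significance tests as a selection criterion.
2. Names in advance sex and a short list of already collected covariates that the investigators judge prognostic. Age and duration of illness are candidates, but the protocol does not rank them.
3. Handles baseline physical activity in one way only: as a covariate with T1 and T2 as the responses (more precise under typical correlations), or as a T0 response. Doing both would put the same measurement on each side of the model.
4. States which GEE contrast is primary.
5. Labels any adjustment prompted by observed imbalance as a sensitivity analysis.

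The randomisation section should also say outright whether allocation is stratified by sex.

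The cost is a few sentences, with no new data and no change to the total of 150. Moving baseline from response to covariate does redefine the response vector and the treatment contrast, so that choice should be made deliberately and before arms are compared.
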